## Abstract

**Introduction:**

Chest pain is one of the most common reasons for contacting the emergency medical services (EMS). It is difficult for EMS personnel to distinguish between patients suffering from a high-risk condition in need of prompt hospital care and patients suitable for non-conveyance. A vast majority of patients with chest pain are therefore transported to the emergency department (ED) for further investigation even if hospital care is not necessary. Improved prehospital assessment and risk stratification, thus accurately and safely identifying patients suitable for non-conveyance, could prevent unnecessary transport to the ED. This would reduce ED crowding and overburdening sparse EMS resources. It would thus also probably reduce healthcare costs. Little is known about the prehospital use of the 5th generation, i.e. high-sensitivity troponin analyses. The aim of this project is to develop an EMS decision support tool using high-sensitivity troponin I for risk assessment of chest pain patients.

**Methods and analysis:**

This is a prospective, multicentre, cohort study including adult unselected EMS patients with chest pain. Data is being collected from 20 May 2023 to 31 December 2025, aiming to include at least 2,000 patients. High-sensitivity troponin I is being analysed bedside using Siemens Healthineers Atellica VTLi. In addition to prehospital troponin I, data is being collected on patient medical history, onset, vital signs, symptoms, ECG and diagnosis at hospital discharge. Several statistical analyses (random forest, logistic regression, gradient boosting) will be conducted to identify the best model for identifying patients with low-risk conditions suitable for non-conveyance.

**Ethics and dissemination:**

The study has been approved by the Swedish Ethical Review Authority (Dnr 2022-01066-01 and 2022-06846-02). Patients are being informed about the study both orally and in writing. The results of the study will be published in a peer-reviewed journal and will be presented at national and/or international conferences.

**Registration details:**

The study is registered at ClinicalTrials.gov (NCT05767619).

**Supplementary Information:**

The online version contains supplementary material available at 10.1186/s13049-024-01314-x.

## Introduction

Emergency medical services (EMS) care has undergone dramatic changes in recent decades. Previously, the EMS focused on quick patient transport to the nearest emergency department (ED) with limited care and assessment on scene. Nowadays, EMS care is more focused on patient assessment and more extensive treatment on scene, thereby enabling non-conveyance or referral to a wide range of different destinations [1]. Therefore, “care at the right level of care” has become a catchphrase. Fast-tracks bypassing the ED, referral to primary care, and remaining on scene with self-care advice are now a natural part of EMS care, in addition to transport to the ED [2]. EMS care has become increasingly differentiated, not solely focusing on the prompt transport of critically ill patients to the nearest ED but also on handling patients with non-urgent care needs.

Chest pain is one of the most common reasons for contacting the EMS [3–5]. However, the above-described methods for differentiating EMS care are generally not available for patients with chest pain. Approximately 15% of EMS chest pain patients have a high-risk condition, for example acute myocardial infarction (AMI), pulmonary embolism or aortic dissection [6, 7]. Of these, fewer than a one-third have an ST-elevation myocardial infarction (STEMI) [6, 8], entitling them to fast-track transportation directly to percutaneous coronary intervention (PCI) centres for immediate revascularisation [9]. The remaining patients with a high-risk condition, suffering mainly from non-ST elevation myocardial infarction (NSTEMI), are transported to often crowded EDs [6]. In the ED, these patients receive further care and investigation along with the 2/3 of all EMS chest pain patients, which often in retrospect, are without need of hospital care, given their diagnosis at hospital discharge [6]. EMS differentiation between patients with time-sensitive conditions and patients without hospital care needs is thus largely deficient. It is difficult for EMS personnel to identify which patients are suffering from a high-risk condition requiring prompt hospital care and which patients are suitable for non-conveyance or referral to primary care. This is the reason why a vast majority of patients with chest pain are transported to the ED for further investigation even if hospital care is not necessary [10]. Furthermore, little is known about chest pain patients which today does not convey [6, 7, 11] and the accuracy of the EMS assessment [11].

In recent years, interest in prehospital analyses of troponins to improve prehospital patient assessment and risk stratification has increased [12–16]. However, these studies used 4th generation troponin analyses, and little is known about the prehospital use of 5th generation, i.e., high-sensitivity troponin analyses. Furthermore, previous studies have focused on the prehospital use of the HEART score even though the HEART score was developed on hospital data for hospital use and does not take high-risk diagnoses other than AMI into account [17]. In addition to prehospital analyses of troponins, the use of artificial intelligence (AI) algorithms [10, 18] and other statistical models has shown promising results regarding the identification of chest pain patients suitable for non-conveyance [17, 19].

Improved prehospital assessment and risk stratification, thus accurately and safely identifying patients suitable for non-conveyance, could prevent unnecessary transport to the ED. It would thus reduce ED crowding and overburdening sparse EMS resources [20]. It would probably also reduce healthcare costs [21, 22]. Furthermore, it would allow patients to avoid unnecessary EMS transport and long waiting times in the ED.

In the BRIAN 1 (BRöstsmärta In AmbulaNs (Swedish), EMS Chest Pain (English)) research programme [6, 17], we previously studied potential improvements in the EMS’ risk stratification of patients with chest pain. We have now started the data collection for BRIAN 2, in which we aim to develop an EMS decision support tool for the risk assessment of chest pain patients using AI and high-sensitivity troponin I. In BRIAN 2, we also aim to validate a previously developed decision support tool from BRIAN 1 [17] and the application of the European Society of Cardiology ESC 0/1 algorithm in the EMS setting [23]. This paper aims to present the study protocol and the initial feasibility of the study.

### Study objectives

To develop a decision support tool for risk stratification of patients with chest pain and validate previously developed decision support tools.

### Scientific questions

To what extent will a developed decision support tool classify patients as low-risk and suitable for non-conveyance?What proportion of patients classified as low-risk will have a high-risk condition upon follow-up?Is a recently developed decision support tool ripe for inclusion in clinical routine?How does the decision support tool compare with existing algorithms and decision support tools for risk prediction in patients with chest pain?

## Methods and analysis

### Study design

Prospective multicentre observational study. Consecutive cases that meet inclusion criteria and lack exclusion criteria for a given period will be included in the study. The study is registered at ClinicalTrials.gov (NCT05767619).

### Population

Adult, unselected, EMS patients with a chief complaint of chest pain as assessed by EMS personnel.

### Inclusion criteria

Chief complaint of chest pain or discomfortPrimary EMS missions, i.e. not EMS transport from or between care facilities

### Exclusion criteria

Age < 18 yearsUnwillingness to participateInability to participate (language barriers, dementia, etc.)

### Setting

Data is being collected at four different sites. All EMS are tax-funded. Each ambulance is staffed by at least one ambulance nurse working with either another ambulance nurse or an emergency medical technician (EMT). Patients with STEMI on the prehospital Electrocardiogram (ECG) are transported directly to the nearest PCI centre, bypassing the ED or hospitals without PCI capabilities.

### Data collection sites

EMS organisation in Göteborg, Lidköping and Uddevalla in Region Västra GötalandEMS organisation in Kungsbacka in Region Halland

### Kungsbacka

Kungsbacka is located in the northern part of Region Halland. The EMS organisation serves approximately 86,000 inhabitants and covers a catchment area of close to 1,500 km^2^. There are five ambulances during the day and three during the night, all manned by at least one registered nurse. There are approximately 600 primary EMS missions involving patients with chest pain annually. As part of routine care, a blood sample is collected during the EMS mission and brought to the ED along with the patient for high-sensitivity troponin T analysis at the hospital laboratory to speed up patient diagnostics at the ED. The results of the troponin analysis are not available to EMS personnel.

Most chest pain patients are transported to the closest regional hospital, located in Varberg, 52 km from Kungsbacka city centre. The hospital in Varberg lacks a PCI laboratory. Patients with STEMI or strongly deviating vital signs are transported to the Sahlgrenska University Hospital, located in Göteborg, 26 km from the Kungsbacka city centre. The Sahlgrenska University Hospital has a PCI laboratory running 24/7.

### Göteborg

Göteborg is the second-largest city in Sweden and is located in the western part of Västra Götaland County. The EMS organisation in Göteborg covers an area of 900 km², serving approximately 700,000 inhabitants. There are 16 ambulances operating during the daytime and 13 during the night, all manned by at least one registered nurse. The EMS system also provides two nurse-staffed single responders and one physician-staffed unit. There are three hospitals in Göteborg to which patients with chest pain are referred and transported, depending on their geographical location. Patients with STEMI or severely deviating vital signs are transported to the Sahlgrenska University Hospital, where it is possible to perform PCI 24/7, after contact with the hospital for a possible fast track/chain of care. There are approximately 45,000 primary EMS missions annually, of which 4,500 involve patients with chest pain.

### Lidköping

Lidköping municipality has an area of 1,400 km^2^ and approximately 40,000 inhabitants. A total of 24,000 of these inhabitants live in the city of Lidköping, which is the main city of Lidköping municipality. The closest hospital is in Skövde, approximately 50 km from Lidköping. The hospital in Skövde has both an ED and a PCI laboratory running 24/7. There are approximately 4,500 EMS missions annually, of which approximately 500 involve patients with chest pain.

### Uddevalla

Uddevalla is located approximately 90 km north of Göteborg. There are approximately 40,000 people living in Uddevalla city and 290,000 people living in the local EMS organisational catchment area. Most EMS patients are transported to NÄL hospital, located 30 km from Uddevalla, with an ED running 24/7. NÄL has a PCI laboratory running from Monday 8 am to Friday 4 pm. For the remaining time, patients with STEMI are referred to the Sahlgrenska University Hospital in Göteborg. There are approximately 4,000 primary EMS missions annually, of which 450 involve patients with chest pain.

### Data collection

Data is being collected from 20 May 2023 to 31 December 2025, aiming to include at least 2,000 patients.

Consecutive sampling is applied. When an EMS unit is assigned a mission concerning a patient with chest pain, the patient is asked by the EMS personnel if they want to participate in the study (informed consent). If so, data collection is initiated on site. The patients also obtain written information regarding the study, allowing them to inform themselves about the study under less stressful circumstances.

Data is being collected on several variables, including demographics, medical history, clinical presentation and symptoms, pain narrative, vital signs, ECG, and troponin, as well as follow-up data on hospital admission, diagnosis and mortality (Supplemental material 1). Variables have mainly been chosen based on the results of BRIAN 1 [6, 17] and other previous studies [8, 9].

Data is being collected using several different data sources. One is the study protocol, which is completed by EMS personnel during the EMS mission. The study protocol includes items regarding clinical presentation, pain narrative, ECG and troponin analyses. Depending on the study site, the study protocol is either integrated into the digital EMS medical records or completed on a separate digital platform (REDCap). Either way, both are filled in during the EMS mission using tablets.

From the EMS medical records, data is being collected regarding vital signs, EMS mission priority, triage and different EMS mission time stamps.

From the hospital medical records, data is being collected regarding age, sex, previous diseases, hospital contact within 72 h of EMS mission, ICD-10 diagnosis, hospital admission and mortality.

The ECG is obtained by the EMS personnel and digitally stored as part of the patient’s medical records. The EMS personnel interpret the ECG on site and state their findings in the study protocol. The ECG will also be interpreted retrospectively by ECG experts when the data collection has been concluded.

Data from the EMS and hospital records is being retrieved using automated data extraction from the data warehouses of the regions included.

Data from the different data sources is being linked together into a single data set used for data analyses using the patients’ personal security number and/or EMS mission event number (Table 1).

**Table 1 Tab1:** Data collection variables

	Definition/description	Data source

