**Demographics and medical history**		
Age	Years	Hospital medical record
Sex	Male/Female	Hospital medical record
Acute coronary syndrome (ACS)	Any of the following ICD-10 codes: I200, I21, I22, I24, I252 or I254	Hospital medical record
Chronic obstructive pulmonary disease (COPD)	Any of the following ICD-10 codes: J44	Hospital medical record
Angina pectoris	Any of the following ICD-10 codes: I201, I208 or I209	Hospital medical record
Hypertension	Any of the following ICD-10 codes: I10, I11, I12, I13 or I15	Hospital medical record
Diabetes mellitus	Any of the following ICD-10 codes: E10, E11 or E14	Hospital medical record
Heart failure	Any of the following ICD-10 codes: I110, I130, I132, I255, I311, I420, I421, I422, I424, I425, I426, I427, I429 or I50	Hospital medical record
Stroke (ischaemic)	Any of the following ICD-10 codes: I63, I64, I65 or I66	Hospital medical record
Renal disease	Any of the following ICD-10 codes: I12, I13, I701, N17, N18, N19, N280, N288 or N289	Hospital medical record
Rheumatism	Any of the following ICD-10 codes: M05 or M06	Hospital medical record
Cancer	Any of the following ICD-10 codes: C1-9	Hospital medical record
Atrial fibrillation/flutter	Any of the following ICD-10 codes: I48	Hospital medical record
Psychiatric diagnosis	Any of the following ICD-10 codes: F1-6	Hospital medical record
Hyperlipidemia	Any of the following ICD-10 codes: E78	Hospital medical record
Previous coronary artery bypass graft (CABG) operation	Any of the following ICD-10 or procedure codes: FNA, FNC, FNE or Z951	Hospital medical record
Previous percutaneous coronary intervention (PCI)	Any of the following ICD-10 or procedure codes: FNG or Z955	Hospital medical record
Smoking	Never smoked; Stopped smoking >1 months ago; Still smoking one month before EMS mission; Unknown	EMS study protocol

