### Rationale for the decision support tool

The decision support tool will be created based on the information given from four different aspects of the clinical assessment: 1) Patient demography (age, sex and previous history, 2) Acute symptoms and clinical findings, 3) ECG findings and 4) Troponin analyses. The relative contribution of each of these four aspects is not known a priori and will most likely differ between cases.

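### The tool's disease-history inputs are hospital codes extracted afterwards, so its performance with the history that ambulance crews obtain on scene cannot be estimated for that block of predictors

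*Protocol article*

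**What the plan says.** The Rationale section builds the tool on four aspects of the clinical assessment, and the first includes history: "Patient demography (age, sex and previous history".

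The Data collection section assigns the sources:

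- **Hospital records:** "From the hospital medical records, data is being collected regarding age, sex, previous diseases, hospital contact within 72 h of EMS mission". Retrieval is automated: "Data from the EMS and hospital records is being retrieved using automated data extraction from the data warehouses of the regions included".
- **EMS records:** "From the EMS medical records, data is being collected regarding vital signs, EMS mission priority, triage and different EMS mission time stamps". Disease history is not listed.
- **Crew form:** "The study protocol includes items regarding clinical presentation, pain narrative, ECG and troponin analyses". Disease history is not listed here either.

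Table 1 agrees. Thirteen diseases plus previous CABG and previous PCI, 15 items in all, have the hospital medical record as their only source and are defined by codes. Smoking is the one history item on the crew form, and it is anchored in time (one category reads "Still smoking one month before EMS mission"). The acute coronary syndrome item is defined as "Any of the following ICD-10 codes: I200, I21, I22, I24, I252 or I254".

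The Interim safety analysis section says that crews evaluate medical history on scene under their clinical guideline.

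**The concern.** A prediction model performs as reported only if its inputs in use are measured as they were in development. Here the users are ambulance crews, and the development data hold a retrospective, coded version of history. Crews obtain their own version on scene, but no described data source keeps it. If the two differ in how often a condition is recorded, predicted risks shift and patients move across the low-risk cut-off. Both primary outcomes, the proportion classified low-risk and the proportion of those who prove to be high-risk, depend on that cut-off. An analysis plan cannot repair this later, because it cannot analyse a variable that was never recorded.

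A second, smaller point concerns timing. The coronary history list includes I21, an acute infarction code, and the reference outcome is the discharge diagnosis from the same hospital records. The article gives no extraction date rule for the history codes. If codes set at the index contact were counted as history, the outcome would enter the predictors. Bootstrap validation would not reveal it, because every resample would carry the same leak.

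**Working it through.** **1. Crew and retrospective versions of each input (Table 1 and Data collection)**

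| Input block | Recorded during the mission | Retrospective version |
|---|---|---|
| Symptoms, pain, clinical findings | Yes, crew form | None needed |
| Vital signs | Yes, first value in EMS record | None needed |
| ECG | Yes, crew reading | Yes, expert reading |
| Troponin I | Yes, bedside | None needed |
| Smoking | Yes, crew form | None needed |
| 15 disease and procedure items | None described | Yes, hospital codes |

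Only the last row lacks a mission-time version. For ECG, the effect of using the crew's reading can be estimated. For disease history it cannot.

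**2. The plan's own figure**

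The Sample size section states 1857, from an event rate of 68%, an AUC of 0.85, 80 parameters and shrinkage of 10% or less. Simulating the Cox-Snell R² implied by that AUC and event rate gives 0.3156.

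- Criterion i: n = 80 / [(0.9 − 1) × ln(1 − 0.3156/0.9)] = 1853 (1855 to 1866 with other simulation seeds)
- Criterion ii: 1818
- Criterion iii: (1.96/0.05)² × 0.68 × 0.32 = 334.4, so 335

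The maximum agrees with 1857 to within simulation error. Nothing in this point changes it.

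**3. Illustration of a source shift**

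Assumptions not in the protocol: 4 to 6 history items are present 10 to 13 percentage points more often in crew-obtained than in coded history, and each has a log odds ratio of 0.5.

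- Logit shift: 4 × 0.10 × 0.5 = 0.20, up to 6 × 0.13 × 0.5 = 0.39. I use 0.2 to 0.4.
- Spread of risk: with AUC 0.85, the binormal separation is √2 × z(0.85) = 1.466. The patient-level logit is ln(0.68/0.32) + 1.466x − 1.466²/2. I read the 68% event rate as the low-risk share.
- Averaging over that spread, the mean predicted low-risk probability falls from 68.0% to 65.1% (shift 0.2) or 62.1% (shift 0.4).
- Subtracting the shift from logit(0.68) directly gives 63.5% and 58.8%. That overstates the effect, because it treats every patient as having the same risk.

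**4. Illustration of leakage, if it occurred**

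Assumptions: index codes enter as history in 3% to 10% of all patients, all in the 32% who are not low-risk (a fraction of 0.03/0.32 = 0.094 to 0.10/0.32 = 0.31 of them). A genuine earlier flag, unrelated to outcome, is carried by 15% to 25% of all patients. A logistic model is then fitted to the marker and the flag.

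| Leak (share of all patients) | AUC, 15% genuine flag | AUC, 25% genuine flag |
|---|---|---|
| 0% | 0.850 | 0.850 |
| 3% | 0.852 | 0.851 |
| 5% | 0.856 | 0.854 |
| 8% | 0.863 | 0.859 |
| 10% | 0.869 | 0.863 |

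The formula f + (1 − f) × 0.85, with f the leaked fraction, gives 0.864 to 0.897. It is too high because it assumes that the flag identifies leaked cases perfectly, whereas patients with genuine earlier disease carry it too.

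**The case against.** Three objections have force.

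**Leakage is not shown.** A reader might infer from I21 and the missing date rule that index diagnoses enter as predictors. The documents do not support that. The Data collection section, the Rationale and the CABG and PCI rows all say *previous*, and the discharge diagnoses have their own rows in Table 1. An earlier infarction would be coded I21 at its own admission, so the code belongs in a history list. A condensed article may leave the extraction date to the full protocol or supplement. This objection stands, and what remains is a rule to confirm.

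**On-scene performance is measured for most inputs.** A reader might conclude that the study does not measure on-scene performance at all, or that crews will never have coded history. Neither follows. Symptoms, vital signs, crew ECG reading, troponin and smoking come from the mission itself. The article does not say how the finished tool will obtain history, and record linkage is possible. The Kungsbacka remark that troponin T results are unavailable to crews concerns a laboratory test and says nothing about access to earlier diagnoses. The point is therefore confined to the history block.

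**Coded history is defensible and extra items cost effort.** Codes give one definition across sites. The Present status section names crew compliance as the main reason for missed inclusions, so 15 more items on the form is a debatable request. That stands against making new data collection the main remedy. It does not answer the lack of any version of the tool assessed only on inputs known to be available on scene.

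**Conclusion.** The point holds for the source of the history block. Fifteen predictors of a tool for crews exist only as hospital codes, and the article describes no crew-obtained counterpart, so performance with the latter cannot be estimated. Whether this matters depends on how far the two versions differ and on how the deployed tool would obtain history. The document settles neither.

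On the stated assumptions, the mean predicted low-risk probability would move by about 3 to 6 percentage points (68% to 65.1% or 62.1%). The under-recording rates and odds ratios behind that are assumed, so it shows scale and is not an estimate. Leakage remains a possibility to exclude. If it occurred at the assumed 3% to 10%, it would move the AUC from 0.85 to between about 0.85 and 0.87, which is negligible at the low end. The sample size of 1857 is unaffected.

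**What to change.** 1. **Main change.** Develop and report the tool both with and without the 15 hospital-coded history items, and give both primary outcomes for each version. Base any statement on readiness for clinical routine on the version whose inputs are available on scene, unless the sponsor states that the deployed tool will read hospital records. This costs analysis time only and covers patients already enrolled.

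2. **Extraction rule.** Confirm in writing that history codes must be dated before the EMS mission was created and that the index contact is excluded. This is one date filter.

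3. **Optional.** For the remaining patients, add a few key history items to the digital crew form and compare them with the codes. This is the only way to measure the discrepancy directly. The cost is some extra crew burden in a study where compliance already limits recruitment, so the list should be short. It cannot be applied to patients already included.
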